**Figure 2 fig2:**
[figure not shown]
Emergency unblinding protocol. HR, heart rate; SBP, systolic blood pressure; IV, intravenous injection.

### Intervention

Upon entering the operating room, the acupuncturist generates a randomization sequence via the Random.org website (https://www.random.org/) to access the corresponding sealed envelope containing group allocation details. Before induction of anesthesia, the acupuncturist applies the assigned thumb-tack devices bilaterally according to the randomized allocation. Both groups receive two thumb-tack devices: a real needle (0.25 mm × 2.0 mm, disposable sterile press needles) and a sham needle with identical appearance but no needle tip. In Group A, the real device is bilaterally applied to the PC6 acupoint – located three finger breadths proximal to the wrist crease between the palmaris longus and flexor carpi radialis tendons – while the sham device is bilaterally positioned at the non-acupoint site six finger breadths proximal to the wrist crease and 2 cm ulnarly. Group B receives the inverse configuration, with sham stimulation bilaterally at PC6 and real stimulation bilaterally at the non-acupoint site. The sham site maintains a 3 cm radius free of established acupoints to prevent collateral stimulation (Figure 3). No deliberate De Qi sensation is elicited during application. Opaque sterile patches will be applied to both intervention sites to conceal the allocation information (Figure 4), with devices remaining *in situ* for 24 postoperative hours. All acupuncture-related procedures are performed in strict accordance with aseptic principles to minimize the risk of infection. Both groups receive standardized PONV prophylaxis per guidelines (18): dexamethasone 5 mg, palonosetron 0.075 mg, propofol target-controlled infusion (TCI) 0.5 μg/mL, and pharyngeal packing.

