**Figure 1 fig1:**
[figure not shown]
Protocol flow. PONV, postoperative nausea and vomiting; QoR-15 score, Quality of Recovery score; PCA, patient-controlled analgesia.

**Table 1 tab1:** Study schedule.

	Screening	Intervention	Operation	Recovery	Follow-up		
Time	The day before operation	Before induction	During surgery	Stay in the recovery room	0–2 h Postoperative	2-6 h Postoperative	6-24 h Postoperative
Eligibility screen	✓						
Informed consent	✓						
Demographic data	✓						
ASA status	✓						
Apfel score	✓						
Randomisation	✓						
PC6 stimulation		✓	✓	✓	✓	✓	✓
Duration of surgery			✓				
Duration of anesthesia			✓				
Duration of controlled hypotension			✓				
Consumption of narcotic drugs			✓				
Extubation time				✓			
NRS score right after extubation				✓			
Duration of PACU stay				✓			
Nausea				✓	✓	✓	✓
Vomiting				✓	✓	✓	✓
Numbers of PCA request							✓
Total PCA volume (mL) delivered							✓
QoR-15 assessment							✓

ASA status, American Society of Anesthesiologists status; NRS, Numerical Rating Scale; PACU, post-anesthesia care unit; PONV, postoperative nausea and vomiting; PCA, patient-controlled analgesia.

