### The principle of randomness

This study will utilize computer-generated block randomization with a total sample size of 216 cases divided into 54 blocks, each containing 4 cases. These blocks are equally allocated to two groups, with sequences randomly arranged within each block. Allocation details will be secured in opaque, sealed envelopes. After obtaining signed informed consent, the acupuncturist administering the intervention will access the randomization sequence through the Random.org website (https://www.random.org/) and then open the corresponding sealed envelope to access group assignment details.

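### The protocol gives three accounts of randomisation that do not fit together, and the unblinded acupuncturist who applies the devices also generates or views the sequence

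*Protocol article*

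**What the plan says.** Four places in the protocol article bear on this.

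- **The principle of randomness** specifies "computer-generated block randomization with a total sample size of 216 cases divided into 54 blocks, each containing 4 cases", and "Allocation details will be secured in opaque, sealed envelopes". Then, once consent is signed, "the acupuncturist administering the intervention will access the randomization sequence through the Random.org website" and opens the matching envelope.
- **Intervention** puts the step in theatre and uses a different verb: on entry to the operating room, "the acupuncturist generates a randomization sequence via the Random.org website", in order to reach the matching envelope.
- **Table 1** ticks the row "Randomisation" in the Screening column, whose time is "The day before operation".
- **Sample size estimation** calls the randomisation stratified with block size 4, names no strata, and arrives at 208 participants. The design sections say 216.

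On roles, attending anesthesiologists recruit on the day before surgery (Subject evaluation, screening and recruitment process). The acupuncturist alone inserts and removes the devices, and a separate coordinator assesses outcomes (Blind method). The Discussion lists participants, anesthesiologists and outcome assessors as blinded. The acupuncturist is not on that list and has to know the arm to place the needles.

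**The concern.** A list fixed in advance in blocks of 4 cannot also be a sequence generated in theatre as each patient arrives, and randomisation on the day before cannot also take place at entry to the operating room. Site staff who follow one section will breach another. The text never says what the Random.org output does: it may display the list, choose an envelope number, or replace the list.

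The second problem is separation of roles. The person who generates or looks up the sequence also opens the envelope and delivers the treatment. At that moment the patient is identified, and sex and approximate age, which the Background names among the predictors of postoperative nausea and vomiting (PONV), are apparent. The primary outcome is any PONV score of 1 or more on a scale of nausea severity, so its baseline risk varies with features that can be seen. What is at stake is independence of assignment from prognosis and, on one reading, the balance over time that blocking is meant to give.

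**Working it through.** **The plan's own figures.** 54 × 4 = 216, so the block count agrees with the enrolment figure in the design sections. The sample size formula, with 0.610, 0.427, one-sided α of 0.05 and power of 0.80, gives 91.02, rounded up to 92 per group, as stated. Allowing for 10% attrition, 92 / 0.9 = 102.2, so 103 per group or 206 in total. The next multiple of 4 is 208, which is 52 blocks. The figures of 208 (52 blocks) and 216 (54 blocks) are each divisible by 4, but they are different lists.

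**Reading 1: the prepared list is used in order.** Assume that each block holds two A and two B, that the block size is known, and that all past allocations are known to the person guessing. There are 6 equally likely blocks (AABB in any order), so 24 positions.

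- Certain assignments: position 4 is always forced, and position 3 is forced when the first two match, which has probability 1/3. That is 1 + 1/3 = 4/3 per block, or 8 of 24 positions = 33.3%. Over 54 blocks, 54 × 4/3 = 72 of 216.
- Correct best guesses: position 1 gives 1/2. Position 2 gives 2/3. Position 3 gives (1/3 × 1) + (2/3 × 1/2) = 2/3. Position 4 gives 1. The sum is 2.833, and 2.833 / 4 = 17/24 = 70.8%, against 50% by chance.

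Knowing only some past allocations would put the success rate between 50% and 70.8%. Seeing the list itself on screen would make every assignment known.

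**Reading 2: a fresh draw picks one of the 216 prepared envelopes, without replacement.** The 33% and 71% figures do not apply, because block position no longer determines what comes next. If every envelope is used, the split is 108:108. During enrolment the blocks have no effect. After 108 patients the number in one arm is hypergeometric with variance 108 × 1/2 × 1/2 × (216 − 108)/(216 − 1) = 13.56, so the arm difference has SD 2 × √13.56 = 7.4. Its simulated 95th percentile is 14. Intact blocks of 4 never allow a difference above 2.

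**Reading 3: the draw replaces the list.** This is simple randomisation. The arm difference at 216 has SD √216 = 14.7. By the exact binomial, the probability of a difference of 10 or more is 0.54, and of 20 or more 0.20.

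The three readings exclude one another, so their consequences must not be added together. What they share is that the treating acupuncturist handles the sequence.

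**The case against.** The strongest reply is that the enrolment decision looks protected. The envelopes are opaque and sealed, the sequence is reached only after consent, the recruiters are anesthesiologists who are not said to see the list, and no section gives the acupuncturist a part in screening or consent. This stands. A reader might infer that allocation is neither concealed nor reproducible, but the document does not show that. Concealment is not assured, which is a weaker statement, and under the randomness section alone a fixed list exists that could be audited.

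Two further inferences are tempting and also unsupported. One is that the acupuncturist could redraw until a preferred envelope appears. If the draw yields only a number and the envelope is sealed, redrawing reveals nothing, and the text does not say what the output shows. The other is that no audit trail exists. Logging of draws and numbering of envelopes are details that an article commonly leaves to the full protocol.

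It is also fair to say that the document speaks of a designated acupuncturist without stating that one person treats all 216 patients, so full knowledge of past allocations is an assumption. Fixed blocks of 4 are not an error in themselves. The primary analysis has no block term, so loss of blocking does not by itself invalidate the test.

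The reply does not remove the contradiction. Nor do separate recruiters protect the interval after consent, when the person handling the sequence has an identified patient at hand.

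**Conclusion.** The point holds in limited form. The randomness section, the Intervention section and Table 1 cannot all be followed as written. On every reading of the first two, sequence handling is not separated from treatment delivery, so concealment from the unblinded acupuncturist is not assured.

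The size depends on the reading. If fixed blocks are used in order and all past allocations are known, 33% of assignments are certain in advance and 71% of best guesses are correct. If a fresh draw picks the envelope, balance during enrolment is no longer held to a difference of 2, although 108:108 is reached if all 216 envelopes are used. If the draw replaces the list, final balance is left to chance as well. Nothing in the document shows that bias has occurred or must occur. The change is worth making because it alters a stated procedure and lowers a real risk at little cost.

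**What to change.** 1. Have someone with no role in recruitment or treatment generate and hold one list before the first patient, or for the remaining patients if enrolment has begun. Preferably use varying block sizes that are not disclosed to site staff.
2. Use sequentially numbered opaque envelopes, opened strictly in enrolment order.
3. Delete the Random.org step from The principle of randomness and from Intervention.
4. State one time for randomisation and make Table 1 agree with it.
5. In Sample size estimation, either name the strata or drop the word stratified, and settle 208 against 216 so that the number of blocks matches the list.

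The cost is a new list and a protocol correction or amendment. The planned start is October 2025, so if patients have already been enrolled, the change of list should be dated and reported. No clinical procedure changes.

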**Figure 3 fig3:**
[figure not shown]
Patients in both groups receive two thumb-tack devices: A real needle (0.25 mm × 2.0 mm) and a sham needle with identical appearance but no needle tip. In Group A, the real device is applied to PC6 point – located three finger breadths proximal to the wrist crease between the palmaris longus and flexor carpi radialis tendons – while the sham device is positioned at a non-acupoint site six finger breadths proximal to the wrist crease and 2 cm ulnarly. Group B receives the inverse configuration, with sham stimulation at PC6 and real stimulation at the non-acupoint site. The sham site maintains a 3 cm radius free of established acupoints to prevent collateral stimulation.

**Figure 4 fig4:**
[figure not shown]
Opaque sterile patches will be applied to both intervention sites to conceal the allocation information.

### Anesthetic management

All patients will undergo standardized preoperative fasting, 8 h for solids, and 3 h for clear fluids. Continuous monitoring will include non-invasive blood pressure, electrocardiogram (ECG), pulse oximetry (SpO_2_), axillary temperature, end-tidal carbon dioxide (EtCO_2_), inspired anesthetic concentrations, and hourly urine output measurement. To enhance external validity and minimize confounding, anesthetic management will be standardized. Anesthesia induction will be achieved with dexamethasone 5 mg IV, propofol TCI 3–4 μg/mL, sufentanil 0.2–0.4 μg/kg, and rocuronium 0.6–0.8 mg/kg. Nasotracheal intubation under direct laryngoscopic guidance initiates mechanical ventilation using a lung-protective strategy: FiO2 40–60%, tidal volume 6 mL/kg predicted body weight, with EtCO_2_ maintained at 35–45 mmHg through respiratory rate adjustment. Maintenance combines propofol TCI 0.5 μg/mL, sevoflurane 1.5–2.5% (minimum alveolar concentration ≥1.0 MAC), remifentanil 0.1–0.2 μg/kg/min, and supplemental rocuronium boluses. Invasive arterial pressure monitoring via radial artery catheterization will be established in the non-dominant upper extremity.

All patients receive intravenous cefuroxime axetil 1.5 g immediately post-induction, with an equivalent prophylactic dose administered 3 h intraoperatively. Axillary temperature maintenance ≥36 °C is ensured using forced-air warming blankets as required. Flurbiprofen 50 mg is administered intravenously 6–7 min prior to surgical skin incision to prevent inflammatory pain. Local infiltration anesthesia with 4% lidocaine containing 1:100,000 epinephrine is applied to both mandibular and maxillary regions. Pharyngeal packing with sterile gauze is implemented to minimize blood ingestion. Controlled hypotension during Le Fort I osteotomy is maintained at a mean arterial pressure (MAP) 50–65 mmHg through combined administration of sevoflurane, metoprolol, and urapidil. Sufentanil 5 μg combining with palonosetron 0.075 mg are administered 30 min prior to surgical closure as preemptive analgesic and antiemetic therapy. Postoperative analgesia was provided via patient-controlled intravenous analgesia (PCIA) using a solution containing sufentanil 100 μg and flurbiprofen 200 mg, diluted with normal saline to a total volume of 100 mL. The pump was programmed with a basal infusion rate of 2 mL/h, a bolus dose of 2 mL, and a lockout interval of 15 min. Neuromuscular blockade reversal with sugammadex is selectively administered based on the patient’s muscle strength recovery. Rescue therapy for refractory PONV consists of intravenous droperidol 1 mg. Supplemental tramadol 100 mg IV is administered if Numerical Rating Scale (NRS; 0 = no pain, 10 = worst pain imaginable) scores exceed 3 points despite three consecutive effective PCIA boluses, with repeat dosing permitted as clinically indicated.

### Data collection and outcome assessment

Following informed consent acquisition, research staff will document baseline parameters including gender, age, height, body weight, body mass index (BMI), history of motion sickness, smoking status, ASA classification, and Apfel risk score (6). Perioperative records will encompass surgical duration, intraoperative fluid balance, controlled hypotension period (defined as MAP <65 mmHg), extubation latency (time from surgery completion to tracheal tube removal), and cumulative dosages of anesthetic agents (propofol, sufentanil, remifentanil).

A designated and trained clinical research specialist will conduct follow-up assessments twice daily (08:00–10:00 and 18:00–20:00) during the initial 24 postoperative hours, evaluating PONV severity, pain intensity, and adverse events. The 12-point PONV assessment scale documents the worst nausea episode per evaluation window, in which 0 = no nausea, 10 = most severe nausea, and 11 = retching/vomiting.

The primary outcome measure of this study is the 24-h incidence of any episode of nausea, vomiting (retching or vomiting) or both (i.e., postoperative nausea and vomiting) postoperatively. PONV is defined as the PONV score ≥1.

Secondary outcomes include: (1) stratified PONV incidence at 0–2 h, 2–6 h, and 6–24 h intervals; (2) peak PONV severity scores during these timeframes; (3) 24-h postoperative QOR-15 score to assess the recovery of patients; (4) the total number of patient-controlled analgesia pump pressed by the patient within 24 h; (5) overall NRS pain score within 24 h; (6) postoperative hospital length of stay; (7) the consumption of tramadol and droperidol.

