**Methods:**

This single-center, double-blind, randomized controlled trial will enroll 216 participants allocated to two groups: group A, the acupoint stimulation group and group B, the sham stimulation group. All subjects will receive standardized PONV prophylaxis including dexamethasone 5 mg IV, palonosetron 0.075 mg IV, target-controlled propofol infusion (0.5 μg/mL), and laryngeal packing following anesthesia induction. Patients in both groups receive two sterile thumb-tack needles – one real needle and one identical-appearing sham needle without a pointed tip. In group A, the real needles are placed at the PC6 acupoint, and the sham needles are placed at the sham acupoint on the forearm. In group B, the real needles are placed at the sham acupoint, while the sham needles are placed on the PC6 acupoint. Finally, all patients will have the sterile opaque patches applied to each acupoint for allocation concealment. The needles will remain in place up to 24 h postoperatively at least. The primary outcome will be the incidence of PONV at 24 h postoperatively. Secondary outcomes will include the incidence rates of PONV at different postoperative intervals and a 15-point quality of life recovery score at 24 h postoperatively.

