### Sample size estimation

Based on existing literature (8), PONV incidence in the control group is estimated to be 61% (p_1_ = 0.610). We anticipate that by minimizing risk strategies and acupoint stimulation, we hypothesize a 30% relative reduction in PONV incidence following bilateral orthognathic surgery [p_2_ = p_1_ × (1–0.3) = 0.610 × 0.7 = 0.427]. The 2020 Fourth Consensus Guidelines for PONV established equivalent efficacy between PC6 acupoint stimulation and pharmacological prophylaxis regarding nausea control, vomiting reduction, and rescue antiemetic requirements. Therefore, this trial aims to assess the combinatorial effect of acupuncture, dexamethasone, and palonosetron on PONV incidence reduction in patients undergoing bilateral orthognathic surgery, using a two independent-sample superiority test for sample size calculation. A one-sided superiority test is employed, with a significance level *α* set at 0.05, and Zα being 1.645. The statistical power (confidence level) is 1-*β*, which is 0.8, and Zβ is 0.84. The sample size per group is calculated using the formula:

$$n=\frac{{\left(Z_{\alpha }\sqrt{2\bar{p}(1-\bar{p})}+Z_{\beta }\sqrt{p_{1}(1-p_{1})+p_{2}(1-p_{2})}\right)}^{2}}{{\left(p_{1}-p_{2}\right)}^{2}}$$

The derived minimum sample size per group is 92 (total *N* = 184). Accounting for 10% attrition and implementing stratified randomization with block size 4, the adjusted final enrollment target reaches 104 participants per group (total *N* = 208).

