### Statistical analysis

The statistical analysis will be performed with the SPSS 25.0 software. Continuous variables are reported as mean ± standard deviation (SD) or median (interquartile range), while categorical variables are expressed as frequencies or percentages. Parametric data were analyzed using ANOVA or the Kruskal-Wallis H-test, whereas nonparametric comparisons employed chi-square tests (*χ*^2^ tests) or Fisher’s exact probability tests. The primary outcome is the 24-h PONV incidence rate. Superiority testing will assess whether the experimental intervention’s efficacy exceeds that of the control group, derived from literature-derived baseline PONV incidence (control group p₁ = 0.610) and hypothesized 30% relative risk reduction (experimental group p₂ = 0.427). The predefined superiority margin (*δ*) is set as an 18.3% absolute risk reduction (i.e., the incidence in the experimental group must be ≤ the incidence in the control group – δ, where *δ* = 0.183). A single-tailed *Z*-test will be used to compare the incidence difference between the two groups, calculating the risk difference (risk difference, RD) with corresponding 97.5% one-sided confidence interval (equivalent to 95% two-sided CI upper bound). Superiority will be established if the CI upper limit for RD remains below *δ*. Relative risk (RR) with 95% CI will supplement these analyses. Nonparametric alternatives (Fisher’s exact test) will substitute when normal approximation assumptions are violated. Post-hoc exploratory analyses are used to examine heterogeneity in the primary outcome across predefined subgroups, including age <25 years, female sex, history of motion sickness/PONV, smoking status, surgery duration >200 min, and hypotension duration >60 min. Logistic regression is employed to adjust for treatment-covariate interactions of subgroup factors. A *p*-value <0.05 will be considered statistically significant. Except for the superiority test, which employs a one-sided test, all other tests are two-sided.

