### Ethics and dissemination plan

The study protocol has undergone tripartite scientific review by the Clinical Research Institute of Peking University Shenzhen Hospital. Four independent clinical experts evaluated the trial’s methodological rigor and operational feasibility. Implementation strictly complies with the Declaration of Helsinki and China’s regulatory requirements for clinical investigations, ensuring ethical integrity and participant safety. Prior to the trial commencement, a comprehensive research plan was meticulously prepared and submitted for rigorous review by the ethics review committee. Following formal approval from the Medical Ethics Committee of Peking University Shenzhen Hospital (approval number: 2025124), the trial achieved prospective registration with the ITMCTR (Trial registration number: ITMCTR2025001713), fulfilling international standards for research transparency.

The participants in this study are patients scheduled for elective surgeries at our institution. On the preoperative day, members of the research team visit each patient at the bedside to provide thorough explanations regarding the objectives and methodology of the study. Prior to obtaining written informed consent, investigators verify participants’ comprehensive understanding of study-related benefits and potential risks. All collected data will use de-identified alphanumeric codes in lieu of personally identifiable information to ensure participant confidentiality during analysis and publication.

Participation in this clinical trial is strictly voluntary. All enrolled subjects retain unconditional rights to withdraw at any stage without compromising their standard perioperative care or incurring therapeutic discrimination. Non-participants and withdrawn cases receive identical evidence-based PONV prophylaxis as per institutional protocols during surgical interventions. The investigative team assumes full financial responsibility for managing study-related adverse events, including emergency medical expenses and extended hospitalization costs attributable to trial participation.

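### QoR-15 is scheduled only at 24 h, with no preoperative score at the existing screening visit, which gives up precision and any description of within-patient change

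*Protocol article*

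**What the plan says.** Under Data collection and outcome assessment, the third secondary outcome is the "24-h postoperative QOR-15 score to assess the recovery of patients". The abstract names two secondary outcomes: PONV incidence by postoperative interval, and "a 15-point quality of life recovery score at 24 h postoperatively", which is evidently the same instrument.

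In Table 1 the row "QoR-15 assessment" has one tick, in the last column (6–24 h postoperative). The Screening column is itemised: eligibility, consent, demographics, ASA status, Apfel score and randomisation are ticked there, and QoR-15 is not. The text agrees with the table. After consent, "research staff will document baseline parameters including gender, age, height, body weight, body mass index (BMI), history of motion sickness, smoking status", followed by ASA class and Apfel score, with no QoR-15.

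The protocol already provides preoperative contact. The Ethics and dissemination plan states: "On the preoperative day, members of the research team visit each patient at the bedside".

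For analysis, the Statistical analysis section says "Parametric data were analyzed using ANOVA or the Kruskal-Wallis H-test" and that, apart from the primary superiority test, "all other tests are two-sided". It describes no baseline-adjusted model for QoR-15 and plans no change from baseline.

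**The concern.** The outcome is meant to describe recovery, yet the only score is taken after surgery. Stable differences between patients in how they score the questionnaire therefore stay in the error term, where a preoperative score would remove part of them. A chance difference between arms in preoperative state also cannot be seen or adjusted for. Nor can the trial report how far patients in either arm stand from their own preoperative score.

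The choice needs attention now because it cannot be reversed. A preoperative score has to be taken before the operation, so each patient enrolled under the present schedule loses it for good. An analysis plan can choose a model, but it cannot supply an uncollected covariate.

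**Working it through.** **Inputs from the documents.** Allocation is 1:1 (Subject evaluation, screening and recruitment process). Tests on secondary outcomes are two-sided, with p < 0.05 as the criterion (Statistical analysis). The protocol gives no standard deviation, effect size, power or sample size for QoR-15. Its only sample size is for PONV, and it is used here just as a realistic number of analysed patients per arm.

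**Reproducing that figure.** The plan states that "PONV incidence in the control group is estimated to be 61" per cent, with p₂ = 0.427, one-sided α = 0.05 (Z = 1.645) and Z_β = 0.84.

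- p̄ = (0.610 + 0.427)/2 = 0.5185
- First term: 1.645 × √(2 × 0.5185 × 0.4815) = 1.162
- Second term: 0.84 × √(0.610 × 0.390 + 0.427 × 0.573) = 0.584
- n = (1.162 + 0.584)² / 0.183² ≈ 91.02, rounded up to 92 per group, as stated

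**Assumed input.** The correlation r between preoperative and 24-h QoR-15 is not in the documents. It is taken as 0.2 to 0.5.

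**Formulas.** Relative to an unadjusted comparison of 24-h scores:

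- ANCOVA with the preoperative score multiplies the variance of the between-arm difference by 1 − r², and its standard error by √(1 − r²).
- The unadjusted sample size giving the same precision is n/(1 − r²).
- A simple change score, with equal variances at the two times, multiplies the variance by 2(1 − r).
- The difference detectable with 80% power at two-sided 5%, unadjusted, at 92 per arm is (1.960 + 0.842) × √(2/92) = 0.413 SD. With adjustment it is 0.413 × √(1 − r²).

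| r | Variance factor 1 − r² | SE reduction | Detectable difference, 92 per arm | Power at 0.413 SD | Unadjusted n per arm for same precision | Change-score variance 2(1 − r) |
|---|---|---|---|---|---|---|
| 0 (unadjusted) | 1.00 | 0% | 0.413 SD | 0.80 | 92 | – |
| 0.2 | 0.96 | 2.0% | 0.405 SD | 0.816 | 96 | 1.6 |
| 0.3 | 0.91 | 4.6% | 0.394 SD | 0.836 | 101 | 1.4 |
| 0.5 | 0.75 | 13.4% | 0.358 SD | 0.899 | 123 | 1.0 |

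The percentage reductions do not depend on the number of patients, so it does not matter here that the article gives both 208 and 216 as the total to enrol.

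**Bias check.** Randomisation makes the expected preoperative score equal in the two arms. The expected between-arm difference in 24-h score therefore equals the expected between-arm difference in change. The missing baseline affects variance, not expectation.

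**The case against.** The strongest reply is that nothing here is wrong. The abstract, Table 1 and the outcome list all define the outcome as a 24-h score, and no section promises change from baseline. That stands: this is a design choice that could be improved, not an error or a contradiction.

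A reader might infer more: that the lone postoperative score confounds the treatment effect with preoperative differences, or that the effect of treatment on loss of recovery cannot be estimated. The documents support neither. Under 1:1 randomisation preoperative differences add noise that the confidence interval already reflects, and the treatment effect on change has the same expectation as the effect on the 24-h score. Only individual change and mean change within each arm are out of reach, and no stated objective needs them.

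The size of the gain rests wholly on an assumed correlation. That also stands. The population is elective, ASA I–II, with psychiatric and central nervous system disorders excluded. This could narrow the spread of preoperative scores and lower r; at r = 0.2 the gain is very small. The gain is also measured against an unadjusted comparison. Sex, age, motion sickness, smoking and Apfel score are already recorded, and if the analysis used them as covariates the added value of a baseline score would differ from r².

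Two replies carry less weight. One is that covariate adjustment is commonly left to an analysis plan, which is not shown. The model may be, but the data collection cannot be. The other is that Table 1 is not a full inventory, since it has no rows for the blinding guess, adverse events or length of stay, and that the baseline list is introduced as non-exhaustive. But QoR-15 does have a row, its Screening cell is blank, and the text agrees. The full protocol could still differ, though the article gives no sign of it.

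**Conclusion.** The point holds as a cheap improvement. The schedule fixes a single 24-h QoR-15 score, and a preoperative score could be had at a visit that already takes place. The cost of leaving it out is a standard error larger than it need be, plus the lack of a descriptive within-patient change. Under the assumed r of 0.2 to 0.5, adjustment would reduce the variance by 4–25% and the standard error by about 2–13%. The direction is certain for any material correlation, but the size cannot be taken from the documents.

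No stated estimand is invalid, the between-arm comparison is not biased by the missing baseline, and the primary outcome and its sample size are untouched. The figures assume a comparison of means, equal variances at the two times for the change-score comparison, and no other covariates in the model.

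**What to change.** 1. Add a tick for QoR-15 in the Screening column of Table 1 and add the score to the baseline data. It should be completed at the bedside visit the day before surgery, after consent and before randomisation. Table 1 places randomisation in that same column, while the Intervention section places it on entry to the operating room. Stating the order explicitly ensures that the questionnaire comes first in either case.
2. State that 24-h QoR-15 will be compared between arms by ANCOVA with the preoperative score as covariate, two-sided.
3. Report change from baseline descriptively only. For r ≤ 0.5 a change score is no more precise than the 24-h score, so testing it would not deliver the gain.

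Cost: a few minutes of each patient's time and one case report form page, with no extra staff, visit or procedure. If enrolment has begun, patients already operated on will have no preoperative score, so the change is worth most if made early.
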